# Effectiveness of a healthcare-based mobile intervention on sedentary patterns, physical activity, mental well-being and clinical and productivity outcomes in office employees with type 2 diabetes: study protocol for a randomized controlled trial

**DOI:** 10.1186/s12889-022-13676-x

**Published:** 2022-06-29

**Keywords:** Mobile applications, Smartphone, Sedentary behaviour, Physical activity, Office employees, Primary healthcare, Diabetes mellitus type 2, Workplace

## Abstract

**Background:**

Prolonged sedentary time is associated with an increased incidence of chronic disease including type 2 diabetes mellitus (DM2). Given that occupational sedentary time contributes significantly to the total amount of daily sedentariness, incorporating programmes to reduce occupational sedentary time in patients with chronic disease would allow for physical, mental and productivity benefits. The aim of this study is to evaluate the short-, medium- and long-term effectiveness of a mHealth programme for sitting less and moving more at work on habitual and occupational sedentary behaviour and physical activity in office staff with DM2. Secondary aims. To evaluate the effectiveness on glycaemic control and lipid profile at 6- and 12-month follow-up; anthropometric profile, blood pressure, mental well-being and work-related post-intervention outcomes at 3, 6 and 12 months.

**Methods:**

Multicentre randomized controlled trial. A sample size of 220 patients will be randomly allocated into a control (*n* = 110) or intervention group (n = 110), with post-intervention follow-ups at 6 and 12 months. Health professionals from Spanish Primary Health Care units will randomly invite patients (18–65 years of age) diagnosed with DM2, who have sedentary office desk-based jobs. The control group will receive usual healthcare and information on the health benefits of sitting less and moving more. The intervention group will receive, through a smartphone app and website, strategies and real-time feedback for 13 weeks to change occupational sedentary behaviour. Variables: (1) Subjective and objective habitual and occupational sedentary behaviour and physical activity (Workforce Sitting Questionnaire, Brief Physical Activity Assessment Tool, activPAL3TM); 2) Glucose, HbA1c; 3) Weight, height, waist circumference; 4) Total, HDL and LDL cholesterol, triglycerides; (5) Systolic, diastolic blood pressure; (6) Mental well-being (Warwick-Edinburgh Mental Well-being); (7) Presenteeism (Work Limitations Questionnaire); (8) Impact of work on employees´ health, sickness absence (6th European Working Conditions Survey); (9) Job-related mental strain (Job Content Questionnaire). Differences between groups pre- and post- intervention on the average value of the variables will be analysed.

**Discussion:**

If the mHealth intervention is effective in reducing sedentary time and increasing physical activity in office employees with DM2, health professionals would have a low-cost tool for the control of patients with chronic disease.

**Trial Registration:**

ClinicalTrials.gov NCT04092738. Registered September 17, 2019.

**Supplementary Information:**

The online version contains supplementary material available at 10.1186/s12889-022-13676-x.

## Background

Sedentary behaviour and physical inactivity are associated with an increased risk of chronic disease [1–3] and all-cause mortality [4, 5]. Prolonged sitting is associated with weight gain and obesity [6], metabolic syndrome [7, 8], cardiovascular disease [5, 9], a higher incidence of DM2 [6, 7, 10] and some types of cancer [11–13]. Excessive sitting is also associated with mental health problems such as lower mental well-being, anxiety and increased risk of depression [14–16]. In modern societies, these unhealthy behaviours contribute to chronic diseases, which progress slowly, appear increasingly early and lead to a loss in quality of life, social labour and health costs [17, 18]. Sedentary behaviour is defined as any activity with a caloric expenditure ≤1.5 Metabolic Equivalent Tasks while remaining in a sitting or reclining posture [19]. Physical inactivity, in turn, is defined as an insufficient physical activity level to meet physical activity recommendations [20]. Sedentary behaviour is a health-related risk factor regardless of physical inactivity [21], which has become very prevalent worldwide due to changes in the physical, social and economic environment [22, 23].

Worldwide, Ding et al. [24] estimated that physical inactivity cost health systems $53.8 billion in 2013. In addition, deaths attributable to physical inactivity cost a further $13.7 billion in lost productivity and resulted in 13.4 million disability-adjusted life years. It was also estimated that sedentary behaviour cost the National Health Service of the United Kingdom (2016–2017) £0.8 billion, which included expenditures on cardiovascular diseases (£424 million), DM2 (£281 million) and colon, lung and endometrial cancers (£56 million) [25]. In spite of that, longitudinal data (2007–2016) on adults from the United States [26] did not observe a significant increase in the adherence rate (63.2 and 65.2% respectively) to the physical activity recommendations (e.g. at least 150 minutes of moderate-intensity or 75 minutes of vigorous-intensity aerobic physical activity per week or some equivalent combination) [20] but a significant increase in sedentary behaviour. The COVID-19 pandemic has promoted physical inactivity and sedentary behaviour [27–29], which had been defined as another pandemic [27, 30] and a major public health problem that must be addressed jointly by healthcare professionals [31].

Although there is no international consensus with regards to healthy sedentary behaviour thresholds for adults, a meta-analysis suggested that adults’ sedentary time should be limited to 7-8 h/day [4]. Other public health guidelines also recommend breaking up sedentary behaviour every 30 minutes [32]. And the World Health Organization (WHO, 2020) [20] suggests that adults should limit the amount of time they spend sedentary.

### Occupational sedentary behaviour, physical inactivity and health

Evidence on the specific health effects of physical activity and sedentary behaviour in the occupational domain are less conclusive [33, 34]. Many adults spend half or more of their day at work, and the hours they spend sitting there make up half of their total sedentary time [35]. Moreover, the COVID-19 pandemic has promoted teleworking and therefore an increase in occupational sedentary behaviour, such as office work at home [36, 37]. Consequently, it is estimated that sedentary time at work would be responsible for 50% of the negative health effects attributable to sedentary behaviour [38].

Additionally, sedentary work time is associated with indicators of productivity and well-being [39], suggesting that “sitting less and moving more” at work could effectively reduce an array of markers of lost productivity [40]. This is especially relevant in people with prevalent chronic disease, who show higher losses of work productivity [41]. “Sitting less and moving more” could also be effective to cope with the increasing levels of work-related stress [42], another current major challenge for people with chronic disease [42, 43]. For all the above, reducing sedentary behaviour at the workplace is a priority area in which to intervene.

Reducing occupational sedentary time by promoting incidental physical activity (such as climbing stairs or walking for short periods) is a key prevention strategy that could help people gradually increase their physical activity levels towards those recommended for optimum health [44, 45]. While numerous health and financial benefits for both employees and employers could be achieved [44, 45], the evidence on effective, long-term intervention strategies in the workplace to reduce sedentary behaviour is limited [46, 47].

### Mobile Health (mHealth) interventions to reduce occupational sedentary behaviour and physical inactivity

Mobile health (mHealth) has been defined as medical and public health practice supported by mobile devices such as mobile phones, patient monitoring devices, and personal digital assistants [48]. mHealth programmes could help change time spent on sedentary behaviour [49–51]. mHealth interventions at work are feasible, acceptable and effective tools for promoting physical activity [49] and reducing sedentary behaviour, even outside working hours [52]. However, studies evaluating the impact of these long-term and specific mHealth programmes on occupational sedentary behaviour are low [49].

Furthermore, the use and efficacy of mHealth programmes mostly focus on healthy adults, without taking into account the impact they might have on specific population groups [53], such as workers with prevalent chronic diseases like obesity or DM2. There is a need for a better understanding of how to integrate mHealth programmes in the self-management of patients with chronic diseases, specifically in the self-management of DM2, and in health care in general [54]. Self-management is fundamental for the well-being of people with DM2 [55, 56] who are mostly treated and managed in primary health care. mHealth interventions as a means of self-management and health promotion offer a promising solution in primary health care to cope with the increasing demand for treatment and control of DM2 [55].

### Healthcare-based mHealth interventions to reduce occupational sedentary behaviour and physical inactivity in people with chronic diseases

Primary health care plays a key role in promoting physical activity and reducing sedentary behaviour for chronic disease. Physical activity is a cost-effective drug that is universally prescribed as first-line treatment, especially to patients with chronic diseases like DM2 [57]. Patients’ physical activity levels and sedentary behaviour reductions can be achieved by using new strategies in clinical practice such as technology including wearables and mHealth programmes. These can be useful for improving treatment adherence and enabling the evaluation and registration of lifestyles in the medical records [57].

### Objectives

In this context, the main objective of this protocol for a randomized controlled trial is to assess the effectiveness in the short-medium and long term of a mHealth programme to “sit less and move more” at work on reducing sedentary behaviour and increasing habitual and work physical activity in office staff with DM2. The secondary objectives are to evaluate the effectiveness of the programme on i) clinical variables: glycaemic control and lipid profile; ii) anthropometric and blood pressure variables; iii) improvement in mental well-being, presenteeism, absenteeism and work-related stress.

This is important given the scarcity of studies that evaluate the effectiveness of mHealth programmes in reducing sedentary behaviour as a therapeutic approach for people with chronic pathology, specifically with DM2, which also evaluate the global health impact of the mHealth intervention on clinical parameters, mental well-being and productivity [46]. This study will make it possible to clarify whether people diagnosed with one of the most prevalent chronic diseases, DM2, are likely to benefit from the implementation of mHealth interventions by healthcare professionals in a wide range of health variables and through the use of objective measures of habitual and occupational sedentary behaviour [49].

### Trial design

This is a prospective, multicentre, two-arm randomized controlled trial with an intervention and control group (i.e. usual care) that will evaluate the effectiveness of an intervention based on a 13-week mHealth programme that aims to replace sedentary work tasks with active ones in office workers with DM2.

## Methods

This study protocol has been developed based on the Standard Protocol Items: Recommendation for Interventional Trials (SPIRIT) guidelines [58].

### Study setting

Data will be collected from primary health care centres in the metropolitan area of Barcelona. This densely populated urban area has a high prevalence of patients with DM2 - in Spain, 7.8% of the adult population have DM2 from which 4.17% belong to the age range of 18–65 years old (5.35% males, 3.28% females) [59] – which ensures easy access to people with this medical condition.

### Recruitment

First, project information will be disseminated to the directors of the primary health care centres in the aforementioned metropolitan area through the Foundation University Institute for Research in Primary Health Care Jordi Gol i Gurina. A meeting with the medical staff of each general practice that shows an interest in volunteering for the project will be organized to recruit physicians and nurses willing to participate in the project. Physicians and nurses that volunteer will sign a written informed consent agreeing to recruit and monitor 5–6 patients for each medical staff unit. Each unit will include one physician and one nurse.

General practices recruitment will be ongoing until enough medical units are reached to achieve the required sample size. In general practices where medical units will participate, a member of the research team will run a two-hour training course with the medical staff that will include: (i) Benefits of physical activity and reduction of sedentary behaviour in DM2; (ii) Information and objectives of the study; (iii) Schedule of the visits and tasks in each follow-up visit. Also, a certified medical professional will provide medical units with a full list of adult patients (18–65 years of age) within their own patients’ portfolio that are diagnosed with DM2 and could potentially participate in the study. Medical units will be advised to ring patients during the first week after the training session, following the list of names order and asking for the inclusion criteria. A specific interview guide for physicians and nurses will be developed to standardize recruitment procedures and identify patients that meet the inclusion criteria.

Patients that meet the inclusion criteria will be invited to participate. If the response is NO, reasons for not volunteering will be recorded in an on-line form (Survey Monkey Enterprise). If the response is YES, more detailed information about the study will be provided and a first appointment with the nurse will be organized in the general practice. In appointment 1, patients will be provided with written detailed information about the study, and if they volunteer they will sign a written informed consent to participate. This process will be repeated until each unit recruits the 5–6 patients agreed (Fig. 1).

**Fig. 1 Fig1:**
[figure not shown]
Recruitment procedure for the Walk@Work-App study protocol of a randomized controlled trial

### Eligibility criteria

Participating patients must be between 18 and 65 years old (working age) and have a mobile phone (smartphone). They must also be diagnosed with DM2 in accordance with international criteria [60], be office workers with a minimum of 55% of their daily working hours performing sedentary tasks according to the Occupational Sitting and Physical Activity Questionnaire (OSPAQ) [61] and have a work contract of at least 18.5 hours.

Furthermore, participants must not (i) have a diagnosis of musculoskeletal, cardiovascular, pulmonary or orthopaedic problems or any other physical condition that prevents them from being physically active; (ii) participate simultaneously in another study or programme of sedentary behaviour, physical activity, nutrition or weight control; (iii) be pregnant; or (iv) have a history of psychiatric problems or substance abuse that could interfere with adherence to the study protocol.

### Allocation

After obtaining the informed consent of the patients to participate in the trial, they will be randomly assigned to the control and intervention group by the research team. The research team will use an Excel file to create a random sequence of numbers allocating patients into two blocks: the control and the intervention group. The sequence of numbers will be the result of a simple randomization process. The research team will randomly provide each medical unit with a series of six numbers to allocate to each patient. After finishing recruiting, the medical unit will allocate one number to each patient and will send this information to the research team.

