### Sample size

Using the free software G*Power [87], the sample size was calculated based on the power of the test and the effect size. Table 2 shows the results for powers of 0.95 and 0.80 and three effect sizes (i.e. small, medium and large). If the intervention and control group are homogenous, the sample size to be taken for a mean effect is 176 in total; 88 patients to the intervention group and 88 to the control group. With a total sample size of 176, the power of the homogeneity test is 0.91 (Table 2).

**Table 2 Tab2:** Power function to test homogeneity of the control and intervention group as a function of the effect size

Effect size (∆*μ* = *d* ∙ *σ*))	Power function
Small (*d* = 0.2) (*n* = 1084, power 0.91)	
Medium (*d* = 0.5) (*n* = 176 power 0.91)	
Large (*d* = 0.5) (*n* = 70 power 0.91)	

It is estimated that on average there is a loss of 20% of patients in clinical trials. If the sample size is increased by this percentage, 220 patients will have to be recruited; 110 in the intervention and 110 in the control group. If the losses do not exceed 20%, a test power of 0.95 would be guaranteed for a mean size effect. If the sample size is not increased at baseline, a loss of 20% would mean having a sample size of 140 patients, which would mean a test power of 0.90. The effect size capable of detecting the test performed with a power of 0.95 or 0.8 shows in additional file 4.

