### Data monitoring

Operating procedures will be documented in a Standard Operating Procedure manual to standardize the administration of trial conditions, data collection methods, tracking procedures, and checking programming into REDCap (e.g. randomization and administration of tools within specified timeline) [88].

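### Simple randomisation, with units matching numbers to patients, does not secure 110:110 or balance within units; a 3:3 block per unit assigned centrally in consent order would come close

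*Protocol article*

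**What the plan says.** The Allocation section first says of consenting patients that "they will be randomly assigned to the control and intervention group by the research team". The team uses Excel to "create a random sequence of numbers allocating patients into two blocks: the control and the intervention group", and "The sequence of numbers will be the result of a simple randomization process". The section continues: "The research team will randomly provide each medical unit with a series of six numbers to allocate to each patient". Then: "After finishing recruiting, the medical unit will allocate one number to each patient and will send this information to the research team". It gives no rule for the order of matching and no restriction within unit.

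The Recruitment section has each unit enrol five or six patients. The Sample size section sets the target: "220 patients will have to be recruited; 110 in the intervention and 110 in the control group". The Blinding section says that kits of identical appearance are supplied after the numbers have been assigned, and that the physician is blinded to group. The Data monitoring section lists, among the procedures to be documented, "checking programming into REDCap (e.g. randomization and administration of tools within specified timeline").

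**The concern.** There are three separate issues.

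- **Target and method do not match.** Equal arms are planned, but simple randomisation fixes only the expected arm size.
- **Units are left to chance.** Patients come in small groups of five or six from units known in advance, which also carry out the follow-up visits. Any difference between units in outcome adds noise to the arm comparison, and balance within unit would remove that noise.
- **The matching step is discretionary and described in two ways.** The research team is said to assign, yet the unit links number to patient in an order of its own choosing. Because six numbers go to a unit that may have five patients, the unit can also choose which number goes unused.

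At stake are a modest amount of precision and an allocation step that can be described and audited without ambiguity. The validity of the trial is not at stake.

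**Working it through.** **The plan's own figure.** Inputs from Sample size and Statistical methods: d = 0.5, power 0.95, one-tailed test, 20% loss. Alpha is not stated; 0.05 is assumed.
- Normal approximation: 2 × (1.645 + 1.645)² / 0.5² = 86.6, so 87 per arm (174 in total).
- The exact noncentral t calculation gives 88 per arm (176), with power 0.951. 176 / 0.8 = 220. The stated 176 and 220 are reproduced.

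**Arm sizes under simple randomisation.** Arm size is Binomial(220, 0.5).
- SD = √(220 × 0.25) = 7.4.
- P(exactly 110) = 0.054.
- 2.5th and 97.5th percentiles: 95 and 125.
- P(arms differ by 20 or more) = 0.20.

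**Cost in power.** Taking the edge of that range, 95:125, and applying 20% loss gives 76:100. Power is 0.948, against 0.951 at 88:88.

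**Split within a unit.**
- Six patients, Binomial(6, 0.5): P(3:3) = 20/64 = 0.3125, so 68.75% are unequal. P(5:1 or worse) = 14/64 = 0.219. P(all one arm) = 2/64 = 0.031.
- Five patients: equality is impossible. P(worse than 3:2) = 1 − 20/32 = 0.375.
- With 36 six-patient units, the expected number unequal is 36 × 0.6875 = 24.75.

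**The other reading of the two blocks.** If the phrase means a fixed list of 110 and 110, the list is balanced overall. Six numbers drawn from it are still 3:3 with probability only 0.317 (hypergeometric), so about 68% of six-patient units remain unequal.

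**Arm sizes with one 3:3 block per unit.** Full units are exactly 3:3, and five-patient units are 3:2 or 2:3. For a total of 220:

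| Mix of units | SD of one arm | 95% range | P(exactly 110:110) |
|---|---|---|---|
| 36 of six, 1 of four | 0.6 | 109–111 | 0.60 |
| 30 of six, 8 of five | 1.4 | 107–113 | 0.28 |
| 20 of six, 20 of five | 2.2 | 106–114 | 0.18 |
| 44 of five | 3.3 | 104–116 | 0.12 |

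**Precision.** Take a six-patient unit, total variance 1 and unit intraclass correlation ρ (assumed 0.05 to 0.10; the article gives none). Under simple randomisation the expected within-unit sum of squares of the arm indicator is E[n₁n₂/6] = 6 × 5 × 0.25 / 6 = 1.25. The total is 6 × 0.25 = 1.5, so 0.25 lies between units. A 3:3 block puts all 1.5 within units. With a random unit effect, information per unit is within/(1 − ρ) + between/(1 + 5ρ):
- ρ = 0.05: simple 1.25/0.95 + 0.25/1.25 = 1.516; block 1.5/0.95 = 1.579. Ratio 0.96, a gain of about 4%.
- ρ = 0.10: simple 1.25/0.90 + 0.25/1.50 = 1.556; block 1.5/0.90 = 1.667. Ratio 0.933, a gain of about 7%.

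**The case against.** Simple randomisation of 220 individuals is a valid method, and 110 per arm can be read as a planning target. The power calculation supports this: overall arm imbalance is immaterial. Most six-patient units (78%) would be 3:3 or 4:2. The planned d = 0.5 is in units of the total SD, so variation between units is already inside the sample size. Outcomes are analysed as change from baseline, which removes stable unit differences, so the true intraclass correlation may be below the assumed range. All of this stands.

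Four stronger readings are tempting, and the documents do not support them.
- A reader might infer that 110:110 cannot occur. It can, with about a 5% chance. If the two blocks mean a fixed list, the list itself is balanced.
- A reader might infer that units can steer patients into an arm. By then the patients have consented, the unit has finished recruiting, and identical-looking kits are still to come. Nothing says that the numbers reveal the arm. Without that knowledge, choosing who gets which number does not steer allocation. Concealment of the code is not spelled out, but an article may leave that to the full protocol.
- A reader might count only within-unit information and put simple randomisation at 1.25/1.5 = 83% of the blocked design. A random unit effect recovers the between-unit part, so the figure is 93 to 96%.
- A reader might see Excel and REDCap as contradictory. A list made in Excel can be loaded into REDCap. The wording merely leaves the link unexplained.

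Blocking also has a cost. Staff who know the block and learn some of a unit's allocations could deduce the others, which bears on the physician's blinding.

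**Conclusion.** The point holds as a design improvement, not as a threat to validity. As written, the allocation does not secure the planned 110:110, and about 69% of six-patient units would be unequal. The unit figure is nearly the same on either reading of the two blocks. The section also leaves the number-to-patient match to the unit while saying that the research team assigns.

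The case rests on balance within unit and on a procedure free of discretion. It does not rest on power: the loss is about 0.3 percentage points, assuming one-sided alpha 0.05. The precision gain of about 4 to 7% applies to full units and depends on the assumed intraclass correlation of 0.05 to 0.10. Blocking narrows the spread of arm sizes (SD from 7.4 to about 0.6–3.3, depending on the mix of unit sizes) but does not guarantee exact equality.

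**What to change.** - Make each unit's six numbers one permuted 3:3 block, so that randomisation is stratified by unit.
- Have the research team assign the numbers in order of consent once the unit has closed recruitment. A five-patient unit uses the first five, so no one chooses which to drop. This step, not the block, removes the discretion. Because recruitment is already closed, predicting the last allocation cannot influence enrolment.
- Include medical unit in the outcome model, for example as a random effect.
- Reword Allocation so that it states who assigns, in what order and under what restriction, what the two blocks mean, and how the list relates to the randomisation mentioned under Data monitoring. Describe 110 per arm as approximate.

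The cost is a new random list and a few sentences. The drawback is possible deduction of allocations within a known block, so the block structure should be held in a restricted document and not disclosed to units.
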